### Optimizing treatment and accessibility

Whereas the combination of CT and CBT-I may be more effective than their use in isolation, and has successfully been applied in only one study [30, 52], no prior study addressed the relative contribution of the different interventions. More research is therefore needed to compare effectiveness of different combinations of therapies; one of the aims of the present study.

A problem facing implementation of CBT-I is the shortage of skilled therapists. Internet-based CBT-I may alleviate this problem [53]. Internet-based therapy is highly self-guided, structured and personalized. Knowledge-based technology renders a personalized concept consult, which can be adjusted by therapist for situations that cannot be pre-programmed. This saves a lot of time for a therapist and subsequently may help to solve the discrepancy between care needed and care available [33, 34], thus allowing for large-scale implementation.

Another opportunity for the optimization of treatment is based on the idea that the people suffering from insomnia most likely represent a heterogeneous mix of subtypes, with different underlying causes and expected treatment response. These subtypes may not only be distinguished by type of sleep problems. Other factors such as personality traits, medical complaints and medical history, the ability to perceive comfort [21, 54–56] may represent variables that differ between the proposed subtypes as well. Our research group commenced a large-scale study using web-based assessment of questionnaires to collect data on these variables (the Netherlands Sleep Registry, NSR, www.sleepregistry.org). The use of latent class analysis on these data will allow for the data-driven detection of multivariate subtypes, calculation of subtype probability for participants according to this data-driven subtype nosology, and evaluation of differential treatment responses, depending on the subtype probability.

The present study aims to evaluate the possibility to optimize insomnia treatment along the principles of personalized and stratified medicine, by making the first step towards the development of a protocol for individualized optimal treatment for specific subtypes of insomnia, which each may show different responsiveness to CBT-I and the different CT manipulations.

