#### Treatment effects and moderation estimates

Mixed effect models will be applied to estimate all time by treatment effects, time by treatment interaction effects and effect moderation by the individual’s insomnia subtype probabilities. For each outcome measure, all effects will be estimated simultaneously in one single linear regression equation. The primary outcome measure of sleep efficiency will be illustrated below. The diary and actigraphy based outcome measures have a two-level hierarchical data-structure: repeated measures of 14 diary inputs *i* across T0 and T1 are nested within subjects *j*. The 14*160 = 2,240 data points can be used to estimate simultaneously all effects ß using the following mixed effect model:$$ \begin{array}{l}\mathrm{S}{\mathrm{E}}_{\mathrm{ij}}\kern0.5em =\kern0.5em {\mathrm{\ss}}_{0\mathrm{i}\mathrm{j}}\kern0.5em +\kern0.5em {\mathrm{\ss}}_1*{\mathrm{Time}}_{\mathrm{ij}}\kern0.5em +\kern0.5em {\mathrm{\ss}}_2*\mathrm{C}\mathrm{B}\mathrm{T}\hbox{-} {\mathrm{I}}_{\mathrm{j}}\kern0.5em +\kern0.5em {\mathrm{\ss}}_3*\mathrm{B}{\mathrm{L}}_{\mathrm{j}}\kern0.5em +\kern0.5em {\mathrm{\ss}}_4*\mathrm{P}{\mathrm{A}}_{\mathrm{j}}\kern0.5em +\kern0.5em {\mathrm{\ss}}_5*\mathrm{B}{\mathrm{W}}_{\mathrm{j}}\kern0.5em +\kern0.5em {\mathrm{\ss}}_6*\mathrm{IS}{\mathrm{P}}_{\mathrm{j}}\kern0.5em +\kern0.5em {\mathrm{\ss}}_7*\mathrm{T}\mathrm{i}\mathrm{m}{\mathrm{e}}_{\mathrm{ij}}*\mathrm{IS}{\mathrm{P}}_{\mathrm{j}}+\\ {}\kern0.5em {\mathbf{\ss}}_{\mathbf{8}}*\mathbf{C}\mathbf{B}\mathbf{T}\hbox{-} {\mathbf{I}}_{\mathbf{j}}*\mathbf{T}\mathbf{i}\mathbf{m}{\mathbf{e}}_{\mathbf{ij}}\kern0.5em +\kern0.5em {\mathrm{\ss}}_9*\mathrm{C}\mathrm{B}\mathrm{T}\hbox{-} \mathrm{I}*\mathrm{IS}{\mathrm{P}}_{\mathrm{j}}\kern0.5em +\kern0.5em {\mathbf{\ss}}_{\mathbf{10}}*\mathbf{C}\mathbf{B}\mathbf{T}\mathbf{\hbox{-} }{\mathbf{I}}_{\mathbf{j}}*\mathbf{T}\mathbf{i}\mathbf{m}{\mathbf{e}}_{\mathbf{ij}}*\mathbf{I}\mathbf{S}\mathbf{P}+\\ {}\kern0.5em {\mathbf{\ss}}_{\mathbf{11}}*\mathbf{B}{\mathbf{L}}_{\mathbf{j}}*\mathbf{T}\mathbf{i}\mathbf{m}{\mathbf{e}}_{\mathbf{ij}}\kern0.5em +\kern0.5em {\mathrm{\ss}}_{12}*\mathrm{B}\mathrm{L}*\mathrm{IS}{\mathrm{P}}_{\mathrm{j}}\kern0.5em +\kern0.5em {\mathbf{\ss}}_{\mathbf{13}}*\mathbf{B}{\mathbf{L}}_{\mathbf{j}}*\mathbf{T}\mathbf{i}\mathbf{m}{\mathbf{e}}_{\mathbf{ij}}*\mathbf{I}\mathbf{S}{\mathbf{P}}_{\mathbf{j}}+\\ {}\kern0.5em {\mathbf{\ss}}_{\mathbf{14}}*\mathbf{P}{\mathbf{A}}_{\mathbf{j}}*\mathbf{T}\mathbf{i}\mathbf{m}{\mathbf{e}}_{\mathbf{ij}}\kern0.5em +\kern0.5em {\mathrm{\ss}}_{15}*\mathrm{P}\mathrm{A}*\mathrm{IS}{\mathrm{P}}_{\mathrm{j}}\kern0.5em +\kern0.5em {\mathbf{\ss}}_{\mathbf{16}}*\mathbf{P}{\mathbf{A}}_{\mathbf{j}}*\mathbf{T}\mathbf{i}\mathbf{m}{\mathbf{e}}_{\mathbf{ij}}*\mathbf{I}\mathbf{S}{\mathbf{P}}_{\mathbf{j}}+\\ {}\kern0.5em {\mathbf{\ss}}_{\mathbf{17}}*\mathbf{B}{\mathbf{W}}_{\mathbf{j}}*\mathbf{T}\mathbf{i}\mathbf{m}{\mathbf{e}}_{\mathbf{ij}}\kern0.5em +\kern0.5em {\mathrm{\ss}}_{18}*\mathrm{B}\mathrm{W}*\mathrm{IS}{\mathrm{P}}_{\mathrm{j}}\kern0.5em +\kern0.5em {\mathbf{\ss}}_{\mathbf{19}}*\mathbf{B}{\mathbf{W}}_{\mathbf{j}}*\mathbf{T}\mathbf{i}\mathbf{m}{\mathbf{e}}_{\mathbf{ij}}*\mathbf{I}\mathbf{S}{\mathbf{P}}_{\mathbf{j}}+\\ {}\kern0.5em {\mathrm{\ss}}_{20}*\mathrm{C}\mathrm{B}\mathrm{T}\hbox{-} {\mathrm{I}}_{\mathrm{j}}*\mathrm{B}{\mathrm{L}}_{\mathrm{j}}\kern0.5em +\kern0.5em {\mathbf{\ss}}_{\mathbf{21}}*\mathbf{C}\mathbf{B}\mathbf{T}\mathbf{\hbox{-} }{\mathbf{I}}_{\mathbf{j}}*\mathbf{B}{\mathbf{L}}_{\mathbf{j}}*\mathbf{T}\mathbf{i}\mathbf{m}{\mathbf{e}}_{\mathbf{ij}}\kern0.5em +\kern0.5em {\mathrm{\ss}}_{22}*\mathrm{C}\mathrm{B}\mathrm{T}\hbox{-} {\mathrm{I}}_{\mathrm{j}}*\mathrm{B}{\mathrm{L}}_{\mathrm{j}}*\mathrm{IS}{\mathrm{P}}_{\mathrm{j}}\kern0.5em +\kern0.5em {\mathbf{\ss}}_{\mathbf{23}}*\mathbf{C}\mathbf{B}\mathbf{T}\hbox{-} \\ {}\kern0.5em {\mathbf{I}}_{\mathbf{j}}*\mathbf{B}{\mathbf{L}}_{\mathbf{j}}*\mathbf{T}\mathbf{i}\mathbf{m}{\mathbf{e}}_{\mathbf{ij}}*\mathbf{I}\mathbf{S}\mathbf{P}+\\ {}\kern0.5em {\mathrm{\ss}}_{24}*\mathrm{C}\mathrm{B}\mathrm{T}\hbox{-} {\mathrm{I}}_{\mathrm{j}}*\mathrm{P}{\mathrm{A}}_{\mathrm{j}}\kern0.5em +\kern0.5em {\mathbf{\ss}}_{\mathbf{25}}*\mathbf{C}\mathbf{B}\mathbf{T}\mathbf{\hbox{-} }{\mathbf{I}}_{\mathbf{j}}*\mathbf{P}{\mathbf{A}}_{\mathbf{j}}*\mathbf{T}\mathbf{i}\mathbf{m}{\mathbf{e}}_{\mathbf{ij}}\kern0.5em +\kern0.5em {\mathrm{\ss}}_{26}*\mathrm{C}\mathrm{B}\mathrm{T}\hbox{-} {\mathrm{I}}_{\mathrm{j}}*\mathrm{P}{\mathrm{A}}_{\mathrm{j}}*\mathrm{IS}{\mathrm{P}}_{\mathrm{j}}\kern0.5em +\kern0.5em {\mathbf{\ss}}_{\mathbf{27}}*\mathbf{C}\mathbf{B}\mathbf{T}\mathbf{\hbox{-}}\\ {}\kern0.5em {\mathbf{I}}_{\mathbf{j}}*\mathbf{P}{\mathbf{A}}_{\mathbf{j}}*\mathbf{T}\mathbf{i}\mathbf{m}{\mathbf{e}}_{\mathbf{ij}}*\mathbf{I}\mathbf{S}\mathbf{P}\mathbf{j}+\\ {}\kern0.5em {\mathrm{\ss}}_{28}*\mathrm{C}\mathrm{B}\mathrm{T}\hbox{-} {\mathrm{I}}_{\mathrm{j}}*\mathrm{B}{\mathrm{W}}_{\mathrm{j}}\kern0.5em +\kern0.5em {\mathbf{\ss}}_{\mathbf{29}}*\mathbf{C}\mathbf{B}\mathbf{T}\mathbf{\hbox{-} }{\mathbf{I}}_{\mathbf{j}}*\mathbf{B}{\mathbf{W}}_{\mathbf{j}}*\mathbf{T}\mathbf{i}\mathbf{m}{\mathbf{e}}_{\mathbf{ij}}\kern0.5em +{\mathrm{\ss}}_{30}*\mathrm{C}\mathrm{B}\mathrm{T}\hbox{-} {\mathrm{I}}_{\mathrm{j}}*\mathrm{B}{\mathrm{W}}_{\mathrm{j}}*\mathrm{IS}{\mathrm{P}}_{\mathrm{j}}\kern0.5em +\kern0.5em {\mathbf{\ss}}_{\mathbf{31}}*\mathbf{C}\mathbf{B}\mathbf{T}\mathbf{\hbox{-}}\\ {}\kern0.5em {\mathbf{I}}_{\mathbf{j}}*\mathbf{B}{\mathbf{W}}_{\mathbf{j}}*\mathbf{T}\mathbf{i}\mathbf{m}{\mathbf{e}}_{\mathbf{ij}}*\mathbf{I}\mathbf{S}{\mathbf{P}}_{\mathbf{j}}\end{array} $$

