
In this regression equation, SE = sleep efficiency; ß_0ij_ = intercept; time denotes the post intervention (T1) versus baseline (T0) assessment week; CBT = cognitive behavior therapy assignment; BL = bright light assignment; PA = physical activity assignment; BW = body warming assignment; ISP = insomnia subtype probability; and ß_1_ to ß_31_ denote effect estimates. The effects and terms of interest are shown in bold font. For example, line 2 shows in bold font the overall treatment by time interaction effect **ß**_**8**_ of CBT-I versus waitlist and the moderation of this effect **ß**_**10**_ by one’s insomnia subtype probability. Lines 3 to 5 show the corresponding effect estimates for BL, PA and BW interventions, and lines 6 to 8 the for their interaction with CBT-I. For clarity, the regression equation shows only one of the four expected ISPs. Wald tests will be used to evaluate the significance of the effect estimates. Statistical significance is thresholded at p = 0.05. The simultaneous estimation of all effects of interest in a single regression model compensates for multiple comparisons. Mixed effect model analyses will be implemented in MLwiN (version 2.02, Centre for Multilevel Modelling, University of Bristol, Bristol, UK.) and (R: A language and evironment for statistical computing, R Foundation for Statistical Computing, Vienna, Austria.).

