### Power and sample size

#### Statistical power estimates

The statistical power of mixed effect regression models with seven repeated measures (diaries) both before and after intervention have been calculated according to the equations given by Twisk, page 280 [90], similar to those calculations made in a previous repeated measures RCT that we published [91]. Statistical power calculations on repeated measures require an estimate of the intraclass correlation coefficient (ICC, that is, within-subject). We estimated the ICC for the primary outcome measure of subjective sleep efficiency from the 9-day sleep diaries [67] that we recently assessed through the internet for 27 people suffering from insomnia according to an Insomnia Severity Index ≥10 [92]. In agreement with the robust observation that night-by-night sleep variability is an intrinsic part of the insomnia symptomatology (reviewed in [88]), we found only a moderate ICC of 0.27, supporting the use of repeated assessment of the primary outcome measure to increase statistical power of the design.

Given this moderate ICC of 0.27, seven pre-assessments at T0, and seven post-assessments at T1, the 160 completing participants provide a power 1-beta of 0.80 to allow for the detection, at a significance of alpha = 0.05, of even small to medium main effects of CBT-I (minimal detectable difference d = 0.27 standard deviations), of each of the three CTs (d = 0.31) and of their interaction with CBT-I (d = 0.41). The minimally detectable difference in the time by treatment interaction between any two types of CT is small to medium as well (d = 0.38).

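### As printed, the diary and actigraphy model has no person-level variation in change, so its Time-by-treatment standard errors are too small whenever people differ in true change beyond treatment and subtype

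*Protocol article*

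**What the plan says.** Under Treatment effects and moderation estimates, the protocol article sets out the model for the primary outcome in full. On the data it says: "The diary and actigraphy based outcome measures have a two-level hierarchical data-structure". The levels are 14 diary nights (seven at T0, seven at T1) and the subject. It adds: "The 14*160 = 2,240 data points can be used to estimate simultaneously all effects".

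In the equation, only the first coefficient has person and night indices. The legend reads: "ß_0ij_ = intercept; time denotes the post intervention (T1) versus baseline (T0) assessment week". The other coefficients have no index, and the legend describes them so: "and ß_1_ to ß_31_ denote effect estimates". The terms marked as being of interest are all Time interactions: CBT-I and each chronobiological treatment (CT) by Time, their combinations, and the same terms by ISP. On testing: "Wald tests will be used to evaluate the significance of the effect estimates". And: "Statistical significance is thresholded at p = 0.05".

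Under Outcome measures, the primary outcome is the change in diary sleep efficiency from week 0 to week 5. Under Statistical power estimates, the authors report on 9-day diaries from 27 people: "we found only a moderate ICC of 0.27".

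**The concern.** Treatment is assigned to persons and the outcome is change. The error for a Time-by-treatment effect should therefore be the between-person variance of change. That variance has two parts: night-to-night noise averaged over each week, and real differences between persons in how far their weekly level moved. In the printed model the person intercept cancels out of the change, and nothing else stands for the second part. Given the intercept, the seven nights of a week count as independent information on that person's change.

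This is valid only if all persons with the same assignment and the same ISP have the same true change. Two things could break that. One is ordinary drift in a person's sleep between two weeks that lie five weeks apart. The other is differing response to treatment, which the article expects of its subtypes: "which each may show different responsiveness to CBT-I and the different CT manipulations". If either is present beyond the modelled terms, confidence intervals are too narrow and the nominal 5% tests reject too often. This applies to the primary outcome and to every other outcome analysed night by night.

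**Working it through.** **Inputs from the article.** 160 completers, so 80 v 80 for CBT-I and 40 per CT condition; seven nights per assessment week; ICC 0.27; alpha 0.05 (taken as two-sided); power 0.80.

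**Inputs assumed.** Total night variance is set to 1, so the night residual is 1 − 0.27 = 0.73. The person-by-week variance *p* and the between-person SD of response *w* are not given and are varied.

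**1. The article's own figures.** The variance of one week's mean is (1 + 6 × 0.27)/7 = 0.374. With d = (1.96 + 0.84) × √[0.374 × (k + 1)/(k × n₁)], where n₁ is the smaller group and k the ratio of the larger to the smaller:

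| Contrast | Groups | Computed | Stated |
|---|---|---|---|
| CBT-I | 80 v 120 − 40 = 80 | 0.271 | 0.27 |
| Each CT | 40 v 120 | 0.313 | 0.31 |
| CT by CBT-I | 20 v 140 | 0.410 | 0.41 |
| Two CTs | 40 v 40 | 0.383 | 0.38 |

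These reproduce. They rest on the variance of a weekly mean, not on the printed model's variance of change. The latter, without person-by-week variance, is 2(0.73)/7 = 0.209 and would give d = 0.202 for CBT-I.

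**2. True variance of one person's change.** 2*p* + 2(0.73)/7.

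**3. Variance that the printed model uses.** A random-intercept model pools 13 within-person degrees of freedom. Twelve lie within weeks and have expectation 0.73. One is the change, with expectation 0.73 + 7*p*. The pooled residual is 0.73 + 7*p*/13, so the model's variance of change is (2/7)(0.73 + 7*p*/13).

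**4. True level of the nominal 5% test.** 2[1 − Φ(1.96 × √(model/true))].

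| *p* | True | Model | True SE / model SE | Type I error |
|---|---|---|---|---|
| 0 | 0.209 | 0.209 | 1.00 | 5% |
| 0.0135 | 0.236 | 0.211 | 1.06 | 6% |
| 0.03 | 0.269 | 0.213 | 1.12 | 8% |
| 0.05 | 0.309 | 0.216 | 1.19 | 10% |
| 0.10 | 0.409 | 0.224 | 1.35 | 15% |
| 0.135 | 0.479 | 0.229 | 1.45 | 17% |

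The last row means that half of the 0.27 is not stable over five weeks.

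**5. Response heterogeneity in the treated arm only.** Averaged over two equal arms it adds *w*²/2 to the true variance and 3.5(*w*²/2)/13 to the pooled residual. For *w* = 0.2, 0.3 and 0.4 the true variances are 0.229, 0.254 and 0.289, against model values of 0.210, 0.212 and 0.215. The levels are about 6%, 7% and 9%. Simulation with 6,000 runs each gave 0.063, 0.070 and 0.093.

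**6. Simulation of drift (80 v 80, 8,000 runs each).** With *p* = 0, 0.027, 0.081 and 0.135, the random-intercept test rejected in 5.4%, 8.3%, 12.3% and 17.6% of runs. An analysis of one change score per person stayed between 4.9% and 5.6%. In one simulated data set with *p* = 0.081, adding a random Time coefficient left the estimate unchanged and moved its standard error from 0.0746 to 0.0947.

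**The case against.** The article never uses the words random intercept and lists no variance components. It presents the equation as an illustration and simplifies it by showing one ISP out of four. A journal article may leave the covariance structure to a fuller plan. What stands of this is that the point concerns the model as printed; a fuller plan could already contain the missing term. But the article gives the complete equation, the number of levels and the test, and its subscripts distinguish the intercept from everything else. The declared simplification covers only the ISPs.

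The model does handle some heterogeneity. Time-by-ISP and treatment-by-Time-by-ISP terms absorb the differences in change that subtype explains, and subtype is where the article locates differing response. This stands: only variation beyond ISP matters.

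A reader might infer that the tests are certainly anti-conservative. The documents do not support that. They give no correlation between week-0 and week-5 levels, and with homogeneous true change the level is 5%. A reader might also place response heterogeneity in both arms, which would give about 7%, 10% and 13% for SD 0.2, 0.3 and 0.4. The article speaks of responsiveness to the treatments, which gives no reason to add the same variance to the untreated arm. If a treatment affects nobody, it adds none at all.

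Finally, a reader might take the power section to be wrong. It is not. Its figures reproduce and use a larger variance (0.374) than the printed model's 0.209. That the ICC comes from a single window is a limit on what it can show, not a contradiction.

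**Conclusion.** The point holds as a conditional one. The omission can only make these standard errors too small; it cannot make them too large. It does so to the extent that persons' true changes vary beyond treatment and ISP. A single 9-day window cannot separate a person's stable level from that week's level, so the ICC of 0.27 gives no assurance that the variation is negligible.

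The size is not fixed by the documents. Over the assumed range of person-by-week variance, 0 to 0.135 of the night variance, the true level of a nominal 5% test runs from 5% to about 17%. Treated-arm response heterogeneity alone gives about 6% to 9%. The calculation assumes balanced groups, complete diaries and otherwise independent nights. The mechanism applies to every Time-by-treatment term, including the CBT-I-by-CT and subtype terms, because each compares change between persons.

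**What to change.** Add a person-level random coefficient for Time, ß_1j = ß_1 + u_1j, with its covariance with the intercept, to the model for the primary outcome and for the other diary and actigraphy outcomes. A subject-by-week level would also serve. The two are close but not identical: the week level forces equal variances in the two weeks, and the unstructured random coefficient does not. State the chosen structure next to the equation.

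The cost is one or two variance parameters in a standard mixed model, and somewhat wider intervals if the heterogeneity is real. For CBT-I at d = 0.27, power with the corrected error would be about 94%, 80% and 69% at person-by-week variance 0.0135, 0.081 and 0.135. The article reports 60 completers and plans to break the treatment code only once the dataset is final, so the change can be made before unblinding.

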### Objectives

The objectives of this study are as follows:

1. To evaluate the relative effectiveness of internet-based CBT-I, three different types of CT (light, temperature and physical activity), and the combined application of CBT-I and each of the CT’s, as compared to placebo treatment, on [1] subjective sleep efficiency (primary outcome), [2] subjective daytime functioning, [3] actigraphic sleep estimates, and [4] cost effectiveness.

2. To evaluate whether insomnia subtype moderates the effectiveness of the individual and the combined treatments.

3. To evaluate whether the effect of CBT-I is enhanced by prior CT.

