## Methods/Design

### Trial design

The study is a double blind, randomized, placebo controlled trial. Aiming at 160 participants who complete the trial, with a dropout rate of 10 %, 180 participants will be recruited, who will be randomly assigned to one of eight limbs in a repeated measures design with two factors (CBT-I and CT), of respectively 2 levels (active CBT-I treatment versus waitlist monitoring) and 4 levels (light, physical activity, body warming and placebo) (see Fig. 1). Covariate-adaptive randomization aims at an equal representation of insomnia subtypes within each treatment limb. Assessment will be performed at baseline (week 0), after a 4-week treatment period (week 5), and after a second 4-week treatment/monitoring period (week 10).

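### Read plainly, the coefficient named as the overall CBT-I effect is a 20 v 20 effect within placebo CT at subtype probability zero, which matches neither its label nor the stated power

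*Protocol article*

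**What the plan says.** Under Trial design, participants are "randomly assigned to one of eight limbs in a repeated measures design with two factors (CBT-I and CT"), CT having "4 levels (light, physical activity, body warming and placebo"). With 160 completers and equal allocation, that is 20 per limb.

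Under Treatment effects and moderation estimates, "For each outcome measure, all effects will be estimated simultaneously in one single linear regression equation". The printed equation has one term each for CBT-I, BL, PA and BW and none for placebo. It also contains the ISP and every product of these with time, up to CBT-I x CT x time x ISP. The regressors are defined as "BL = bright light assignment; PA = physical activity assignment; BW = body warming assignment; ISP = insomnia subtype probability". The text then interprets the coefficients: "line 2 shows in bold font the overall treatment by time interaction effect" (ß8), and "Lines 3 to 5 show the corresponding effect estimates for BL, PA and BW interventions" (ß11, ß14, ß17). Significance is judged by Wald tests of the effect estimates at 0.05.

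Under Statistical power estimates, 160 completers give 80% power for a CBT-I main effect ("minimal detectable difference d = 0.27 standard deviations"), for each CT (0.31) and for a CT v CT difference (0.38).

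Objective 1 asks for the effects of CBT-I, each CT and each combination "as compared to placebo treatment, on [1] subjective sleep efficiency (primary outcome").

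**The concern.** In a model with interactions, a lower-order coefficient is the effect where every other variable in its products equals zero. If CBT-I and the CTs enter as 0/1 assignment indicators and the ISP as a raw probability, zero means placebo CT (for ß8) or waitlist (for ß11, ß14 and ß17), and in all four cases a subtype probability of zero. A Wald test of ß8 would then not test the averaged effect that its label promises, and none of the four tests would use the comparisons for which power is stated. An analyst following the article literally could report a result from one corner of the factorial design as the overall effect, with much less precision than stated.

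**Working it through.** **What ß8 is.** Collect the time terms of the printed equation. The CBT-I v waitlist effect on change is

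ß8 + ß10·ISP + BL(ß21 + ß23·ISP) + PA(ß25 + ß27·ISP) + BW(ß29 + ß31·ISP).

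With 0/1 indicators and a raw ISP, this reduces to ß8 only when BL = PA = BW = 0 (placebo CT) and ISP = 0. Averaged over the four CT levels at mean ISP m, it is

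ß8 + m·ß10 + ¼[(ß21 + ß25 + ß29) + m(ß23 + ß27 + ß31)].

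The two agree in general only if the added terms cancel or vanish. Similarly, ß11 is BL v placebo on the waitlist at ISP = 0, whereas the average over CBT-I is ß11 + ½ß21 + m(ß13 + ½ß23). PA and BW follow the same pattern.

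**Numerical check.** The 32-column design (8 limbs of 20, 0/1 indicators, raw ISP) has full rank. It was fitted to noise-free data with CBT-I effects of 2, 6, 8 and 10 in placebo, BL, PA and BW, plus 4 x ISP. The fit gave ß8 = 2.0. The average effect is (2 + 6 + 8 + 10)/4 + 4 x 0.25 = 7.5. The six BL, PA and BW limbs had zero weight in ß8.

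**The plan's own power figures.** Inputs from Statistical power estimates: ICC 0.27, seven nights per assessment, alpha 0.05 (taken as two-sided), power 0.80, 160 completers.

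d = sqrt[(1.960 + 0.842)² x V x (1/n1 + 1/n2)], with V = (1 + 6 x 0.27)/7 = 0.3743.

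- CBT-I, 80 v 80: 0.271 (stated 0.27)
- Each CT, 40 v 120: 0.313 (stated 0.31)
- CT v CT, 40 v 40: 0.383 (stated 0.38)

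The 0.31 thus compares one CT with everyone else, including the other active CTs. CT v placebo averaged over CBT-I is 40 v 40, or 0.38.

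**The coefficients as written.** For 20 v 20, d = sqrt[7.849 x 0.3743 x 0.1] = 0.54. This is twice the 80 v 80 figure whatever the variance, because sqrt(80/20) = 2. Power at d = 0.27: the SE is sqrt(0.3743 x 0.1) = 0.193, 0.27/0.193 - 1.96 is about -0.56, and power is 29%. At d = 0.31 it is 36%.

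As a sensitivity check, take the variance of a change score with constant ICC, 2(1 - 0.27)/7 = 0.2086. Then the detectable d at 20 v 20 is 0.40, and power is 46% at 0.27 and 57% at 0.31.

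**Evaluating at ISP = 0.** This multiplies the variance by about 1 + mean²/var(ISP). Four subtypes of about equal prevalence (Effect moderation by subtype score) imply a mean near 0.25. The spread is not given. For one ISP, with the variance assumed to lie between 0.1875 (almost crisp classes) and 0.05:

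- factor: 1.33 to 2.25
- detectable d: 0.63 to 0.81 (0.47 to 0.61 with change-score variance)
- power at d = 0.27 under the plan's variance: 23% to 15%

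These figures only illustrate the direction and possible size of the loss.

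**The case against.** The strongest reply is that the article never states 0/1 coding or an uncentred ISP. The equation is offered as an illustration and shows one ISP of four for brevity. Coding is often left to an analysis plan, and the stated intention is an overall effect. With ±½ coding for CBT-I, centred CT terms and a mean-centred ISP, ß8 would be just that. This stands as a limit on the claim: the coding is the plain reading of assignment terms with placebo omitted, not a stated fact. It does not remove the point, because the article prints the model, names the coefficients, interprets them and attaches the tests. Two unstated choices, coding and centring, are both needed to make the label true.

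A reader might also infer that the tests answer a different question from Objective 1. The documents do not support that. Apart from ISP = 0, CBT-I alone and each CT alone against waitlist plus placebo are a natural reading of a comparison with placebo. The conflict is with the word overall and with the power section.

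Nor does the model throw away the factorial information. The fit is the same under either coding, and every averaged or combined contrast can be drawn from it. The fault lies in which coefficient is named and tested.

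**Conclusion.** The point holds, conditional on 0/1 indicators and a raw ISP. On that reading ß8 is not the overall effect claimed, and ß8, ß11, ß14 and ß17 do not correspond to the comparisons behind 0.27 and 0.31. The firm size is a detectable d of 0.54 (0.40 with change-score variance) and power of 29% (46%) at d = 0.27. It assumes 20 completers per limb and ignores the ISP. The further loss at ISP = 0 is real but cannot be sized, because the spread of the ISPs is unknown.

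It would be tempting to conclude that a true CBT-I effect would probably be missed. The documents do not support this: 0.27 is a minimal detectable difference, no expected effect is given, and the shortfall matters mainly for small effects. Correcting the coding also does not recover 0.31 for a CT v placebo, since that figure used a different comparator.

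**What to change.** Keep the model and state its parameterisation: CBT-I as ±0.5, each CT indicator minus ¼, each ISP minus its mean. Then ß8 is CBT-I v waitlist averaged over CT levels, and ß11, ß14 and ß17 are each CT v placebo averaged over CBT-I, all at mean ISP. Equivalently, keep 0/1 coding and pre-specify those averaged contrasts as the Wald-tested effects.

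For the combinations in Objective 1, add a linear combination for each CBT-I + CT cell v waitlist + placebo. In 0/1 coding at ISP = 0 this is ß8 + ß11 + ß21 for bright light, and analogously for the others; at mean ISP the matching ISP products are added.

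Restate the CT v placebo detectable difference as about 0.38 (40 v 40).

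If simple effects are intended instead, drop the word overall and give detectable differences for 20 v 20.

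The cost is a few sentences and lines of code, with no new data. The change can be made while the treatment codes are still unbroken.

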## Abstract

**Background:**

DSM-V criteria for insomnia disorder are met by 6 to 10 % of the adult population. Insomnia has severe consequences for health and society. One of the most common treatments provided by primary caregivers is pharmacological treatment, which is far from optimal and has not been recommended since a 2005 consensus report of the National Institutes of Health. The recommended treatment is Cognitive Behavioral Therapy for Insomnia. Effectiveness, however, is still limited. Only a few studies have evaluated the effectiveness of chronobiological treatments, including the timed application of bright light, physical activity and body warming. Another opportunity for optimization of treatment is based on the idea that the people suffering from insomnia most likely represent a heterogeneous mix of subtypes, with different underlying causes and expected treatment responses.

The present study aims to evaluate the possibility for optimizing insomnia treatment along the principles of personalized and stratified medicine. It evaluates the following:The relative effectiveness of internet-supported cognitive behavioral therapy, bright light, physical activity and body warming;Whether the effectiveness of internet-supported cognitive behavioral therapy for insomnia can be augmented by simultaneous or prior application of bright light, physical activity and body warming; andWhether the effectiveness of the interventions and their combination are moderated by the insomnia subtype.

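### For CBT-I combined with CT, the named tests address departure from additivity only; no test is named for the combination against placebo or against CBT-I plus placebo

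*Protocol article*

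**What the plan says.** The abstract asks "Whether the effectiveness of internet-supported cognitive behavioral therapy for insomnia can be augmented by simultaneous or prior application of bright light", physical activity (PA) or body warming (BW). The background section on optimizing treatment gives the motive, "Whereas the combination of CT and CBT-I may be more effective than their use in isolation", and makes comparing combinations one of the aims. Objective 1 lists CBT-I, each CT and each combination, "as compared to placebo treatment", with subjective sleep efficiency as primary outcome.

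The section on treatment effects and moderation estimates fits one mixed model to the T0 and T1 diaries. It states that "The effects and terms of interest are shown in bold font", that "Wald tests will be used to evaluate the significance of the effect estimates", and that "Statistical significance is thresholded at p = 0.05". The bold terms without subtype moderation are the single-treatment by time terms (ß8 for CBT-I, ß11 for bright light (BL), ß14 for PA, ß17 for BW) and the CBT-I by CT by time products (ß21, ß25, ß29). Each also has a version moderated by insomnia subtype probability (ISP). The text introduces the products as "and lines 6 to 8 the for their interaction with CBT-I". It names no sum of coefficients.

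**The concern.** A product term and a combination contrast answer different questions. The null of ß21 is that CBT-I plus light changes sleep efficiency by exactly the sum of what each does alone. Objective 1 asks whether the combination differs from placebo, and the augmentation aim, on one natural reading, asks whether adding light to CBT-I gives more than CBT-I with placebo. Neither is a coefficient in the list of terms of interest. If the benefits simply add, ß21 is zero. A report built on the listed coefficients would then contain no direct test of the combination on the primary outcome, and a non-significant product could be taken as an answer to a question it does not address.

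**Working it through.** **Inputs.** From the trial design and power sections: 160 completers in eight limbs (20 per limb if allocation is equal), seven diaries before and seven after, ICC 0.27, alpha 0.05, power 0.80. Assumed: two-sided tests (z sum 1.960 + 0.842 = 2.802) and no ISP terms in the arithmetic.

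**1. The plan's own figures.** The variance factor for a seven-diary mean is (1 + 6 × 0.27)/7 = 0.3743, and d = 2.802 × √[0.3743 × (1/n1 + 1/n2)].
- 80 v 80: 0.271 (stated 0.27, CBT-I)
- 40 v 120: 0.313 (stated 0.31, each CT)
- 40 v 40: 0.383 (stated 0.38, two CTs)
- 20 v 140: 0.410 (stated 0.41, interaction)

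All four reproduce. The interaction figure does so as one combined limb against everyone else, which is not the product term in the model.

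**2. What each coefficient tests.** Modelled T0 to T1 change in 0/1 coding, shown for BL:

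| Limb | Change |
|---|---|
| Waitlist + placebo | ß1 |
| Waitlist + BL | ß1 + ß11 |
| CBT-I + placebo | ß1 + ß8 |
| CBT-I + BL | ß1 + ß8 + ß11 + ß21 |

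By subtraction:
- combination v placebo = ß8 + ß11 + ß21
- combination v CBT-I + placebo = ß11 + ß21
- combination v BL alone = ß8 + ß21
- ß11 = BL v placebo in the waitlist limbs only
- ß21 = the difference between the BL effect with CBT-I and the BL effect without it

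**3. Product term under additivity.** Then ß21 = 0, so its test rejects at alpha, 5%, whatever the size of the benefit. A simulation of the 2 × 4 design (6,000 trials per scenario) gave 5.2% to 5.4% for one product and about 13% for at least one of the three.

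**4. Precision on the protocol's variance.** A contrast of two limbs has SE = √(0.3743 × 2/20) = 0.193.
- Detectable d at 80% power: 2.802 × 0.193 = 0.54
- Power at d = 0.31: Φ(0.31/0.193 − 1.96) = 36%
- Power at d = 0.41: Φ(0.41/0.193 − 1.96) = 56%

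The product term uses four limbs: SE = √(0.3743 × 4/20) = 0.274, detectable d = 0.77.

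**5. Precision with the subject intercept differenced out.** The variance of the change is 2 × (1 − 0.27)/7 = 0.2086.
- Two-limb contrast: SE = √(0.2086 × 2/20) = 0.144, detectable d = 0.40, power at d = 0.41 about 81%
- Product term: SE = √(0.2086 × 4/20) = 0.204, detectable d = 0.57

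**6. ISP terms.** With them in the model, the gain from adding BL to CBT-I at subtype probability p is ß11 + ß21 + (ß13 + ß23) × p. With uncentred ISPs, the plain sum ß11 + ß21 is therefore the effect at p = 0, not the average effect.

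**The case against.** The strongest reply has four parts.

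First, the article writes down no null hypothesis. Asking whether the effectiveness of CBT-I can be augmented may mean effect modification, which is what the products test. This stands for the augmentation aim, but it does not supply the comparison with placebo in objective 1.

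Second, a reader might infer that the plan would miss an additive combined benefit 95% of the time. The documents do not support that. The 95% is 1 − alpha for one coefficient assumed to be zero. In the same scenario ß11 is also tested, and in 0/1 coding it has the same SE, hence the same power, as ß11 + ß21. The article calls ß8 an overall effect and speaks of main effects, so coefficients averaged over the other factor are also a possible reading. An averaged BL effect compares 40 with 40 and has 62% power at d = 0.31 on the protocol's variance. Still, it is not the effect of BL among CBT-I users.

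Third, a reader might go on to predict false claims of augmentation, or of light harming CBT-I. Those need a decision rule, such as reading a significant ß11 with a non-significant ß21 as augmentation. The article states no such rule.

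Fourth, the sums are estimable from the model, the power section already sizes a comparison of two CTs that is not a bold term, and a condensed article may leave derived contrasts to a fuller document. The estimability point stands, and it makes the repair simple. But the article does fix the equation, the terms of interest and the test, and within that list the combination is represented only by products.

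**Conclusion.** The point holds as a mismatch between objective and named test, not as a defect of the model. For simultaneous treatment, the only combination terms named and tested measure synergy or antagonism. The comparison of each combination with placebo, which objective 1 sets for the primary outcome, and the gain over CBT-I plus placebo have no named test. Under pure additivity each product test rejects 5% of the time. The CT benefit remains visible through ß11, ß14 and ß17, but in 0/1 coding only for the waitlist limbs, so carry-over to CBT-I users is not directly tested.

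Power for the missing contrasts depends on the variance: 56% at d = 0.41 on the protocol's own basis, about 81% if the subject intercept is differenced out. These figures assume 20 completers per limb, two-sided tests and no ISP terms. The point covers simultaneous treatment only; the aim about prior CT lies outside this T0 to T1 model.

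**What to change.** State whether augmentation means any added benefit or a more-than-additive benefit. Keep the single model and prespecify, for each CT:
- combination v placebo: ß8 + ß11 + ß21 for BL; ß8 + ß14 + ß25 for PA; ß8 + ß17 + ß29 for BW
- combination v CBT-I + placebo: ß11 + ß21; ß14 + ß25; ß17 + ß29
- combination v CT alone: ß8 + ß21; ß8 + ß25; ß8 + ß29

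State the 0/1 coding, and evaluate the contrasts with the ISPs centred or averaged over the sample. Report ß21, ß25 and ß29 with confidence intervals as tests of synergy only. Give the precision of the two-limb contrasts (about d = 0.54, or 0.40 differenced, for 80% power), and say which comparison the stated interaction figure of 0.41 refers to.

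The cost is a few lines of text and Wald contrasts from a model that will be fitted anyway, with no new data or participants. The small downside is a few more contrasts to place in the multiplicity plan. The article reports recruitment as ongoing and the treatment code as held until the dataset is final, so the contrasts can be named before anyone sees results by treatment.
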